## Abstract

**Introduction:**

Person-centred prescription (PCP) is a medication revision based on patients’ frailty status and diagnostic- and drug-centred criteria. This pragmatic trial aims to implement and evaluate a multidimensional PCP intervention to improve pharmacological treatment adequacy in older adults admitted to an intermediate care hospital (ICH), following a mixed-method approach.

**Description:**

The “Applying a Multidisciplinary Intervention for Drug Adequacy-ICH” (AMIDA-ICH) study follows a hybrid design. Five hospital wards will enter the intervention phase following a stepped–wedge randomized clinical trial design. Subjects belonging to the control phase will receive usual care; those belonging to the intervention phase will undergo a multidisciplinary PCP. We will evaluate the intervention’s impact on reducing medications and improving treatment adequacy, patient-reported outcome measures, and health outcomes, such as adverse events, hospital admissions, and mortality. Finally, the qualitative part will involve professionals, patients, and carers with the aim of identifying barriers and enablers to implement the intervention.

**Discussion:**

This study is designed to improve therapeutic adequacy and quality of care in older adults through a PCP approach. It focuses on outcomes like efficacy and safety, while also assessing the real-world applicability of the intervention through implementation outcomes.

**Clinical trial registration:**

https://clinicaltrials.gov/study/NCT07015112, NCT07015112.

## Highlights

Hybrid mixed-methods design combining a stepped-wedge cluster randomized trial with qualitative evaluationMultidisciplinary person-centred prescription model, based on frailtyEvaluation of medication appropriateness and key clinical outcomes, including adverse events, readmissions and mortalitySingle-center study, which may limit the generalisability of findings.

## Introduction

The current demographic landscape is characterized by increased life expectancy (1), driven by a genetic background on which lifestyle and environment have significant weight (1). Nonetheless, it does not appear to be mirrored by an equally significant increase in healthy life expectancy (1, 2).

The concept of frailty has therefore become increasingly relevant in the literature as well as in clinical practice, as it highlights the complex interplay of factors called into question in driving treatment intensity and goals of care in the older population.

Frailty has not a universally shared definition, although it is commonly described as a dynamic, age-related, multidimensional “biopsychosocial” syndrome, characterized by declined functioning in different geriatric domains, and increased vulnerability to stressors (3, 4). It is also defined as a state of poor health deriving from the accumulation of deficits, rather than a syndrome (5). Whatever the definition, it represents a significant public health concern, making patients more vulnerable to complications, disability and a higher risk of institutionalization (4). A systematic review of 240 population-based studies, including almost 1,800,000 community-dwelling people over 62 countries, aged 50 years and older, showed that the prevalence of frailty as a “physical syndrome” is around 12%, while frailty as a deficit accumulation is around 24% (6). Frailty also seems to depend on the number of chronic diseases (7), and excluding patients with multiple diseases and higher degrees of frailty from clinical trials surely represents a limitation of the scientific literature and the clinical practice as well.

Moreover, a significant comorbidity burden usually involves a just as significant medication burden. The term “polypharmacy” arises in this context, being recognized as a geriatric syndrome. As for frailty, polypharmacy does not have a commonly shared definition. It usually refers to the chronic need for 5 or more medications (8), but some other definitions have been proposed in the literature. Some works also consider the duration of the treatment or qualitative criteria (8). This suggests that, regardless of the mere quantity, certain medications may be inadequate and potentially inappropriate in certain specific population groups. A systematic review of 106 observational studies on young and older adults showed a pooled polypharmacy prevalence of 37%, regardless of the definition (9). This review included inpatients, as well as outpatients and community-dwelling people, demonstrating the association between polypharmacy and age (65 years and older), and also clinical setting – related to the level of intensity of care –, but not with geography nor gender (9). Polypharmacy and frailty appear to be mutually related. A secondary analysis of a large randomized-controlled trial conducted in US and Australia showed that people chronically taking 5 or more medications had a relative risk ratio of 1.15 for pre-frailty and 3.34 for frailty, and that polypharmacy increased the disability-free survival period loss in both pre-frail and frail people (10). Several authors suggest that the relationship between polypharmacy and frailty is bidirectional (7, 11, 12). Although most of the studies are not designed to determine this association, it seems that medications can influence frailty and are directly involved in its pathogenesis (7, 12). Moreover, this link remains also when considering frailty and potentially inappropriate medications (PIMs) (11), anticholinergic burden, and adverse drug events (ADEs) (12). Also, despite the prevalence of polypharmacy increasing worldwide, there is still a high prevalence of underprescription in the older population, which might contribute to the negative consequences of inappropriate prescription (13).

Multiple tools are available to assist clinicians with the process of medication optimization, the majority of which are explicit, that is lists of medications that should not be prescribed in older people because of an unfavorable benefit–risk profile (14), and, for some of them, lists of medication that should be prescribed because of a valid indication, such as the STOPP and START criteria (6). Although widespread and useful, they cannot fully address all the heterogeneity displayed by the older adult population. For these reasons, other strategies should be implemented. According to available evidence in older patients with polypharmacy, the medication review is a key strategy (12, 15). It is explained that the revision faces patient-, provider- and system-based barriers, and even if it may have no significant impact on mortality or ADEs, it can improve the quality of life, increase deprescription, and reduce health costs and readmissions (12, 16). In particular, an evidence-based approach such as person-centred prescription (PCP) should be recommended. It refers to a multiprofessional approach aimed at improving the quality of care. The literature offers some models, implemented in different countries and contexts, and the role of the patients is always crucial (17, 18). These models consider individual characteristics to enhance appropriate medication use, adherence, and safety, with different instruments (16, 19, 20). Generally speaking, to achieve it, in response to a “medication-oriented” approach, PCP focuses more on subjective clinical context. Moreover, in this regard, therapeutic plans should be agreed with the patients and their caregivers (21, 22).

There is growing interest in enhancing patient care through more seamless transitions and support systems. In the realm of continuity of care, intermediate care services represent transitional time-limited services which ensure continuity of care, promote recovery, independence and confidence at the interface between home and acute services (23, 24), thus shortening or avoiding unnecessary admissions to acute wards, even with debated efficacy (24).

### Problem statement

Although PCP should be considered for all older frail patients, its implementation is often challenging in certain settings due to structural limitations, a predominantly disease-oriented approach, and/or limited time. Intermediate Care Hospitals (ICHs) may offer an optimal environment for conducting patient-centred medication reviews, for several reasons. Multidisciplinary teams, including geriatricians, nurses, pharmacists, physiotherapists, occupational therapists, and social workers, among others, operate in ICH. Comprehensive geriatric assessment, enablement and rehabilitation are implemented, with a focus on optimizing recovery and independence, and, when possible, improving frailty status after an acute event. Moreover, the relatively extended stay of patients supports a more thorough and multidimensional approach to “functional recovery.” Nonetheless, despite representing an ideal environment, evidence on the patient-centred prescription process in ICH is still lacking.

Given the above-mentioned background, the implementation of an intervention based on PCP review by a multidisciplinary team (geriatrician, clinical pharmacist, nurse) might improve the adequacy of treatments and reduce the level of polypharmacy in the older population admitted to ICHs. Also, the inclusion of patient views and preferences regarding their treatment during the PCP review might help to achieve success in reducing polypharmacy, i.e., deprescribing, and improving adherence (25). The goal of the intervention is therefore to maximize benefits of pharmacological treatment, and concurrently reduce medication-related risks, such as ADEs.

### Objectives

The objective of this trial is the implementation of a multidimensional intervention addressed at improving adequacy of pharmacological treatment in older adults admitted to an ICH.

Different dimensions of the proposed intervention will be assessed in parallel. We will evaluate the impact of the intervention on reducing the number of medications per patient and polypharmacy prevalence, and on the adequacy and safety of treatments, including ADEs, unplanned readmissions, and mortality. We will also evaluate patients’ preferences and attitudes towards pharmacological treatment during the medication review process, together with barriers and enablers for the implementation of the intervention.

## Description of the methodology

### Design

This study will follow a type 2 hybrid design (26) to implement and evaluate a complex intervention, using mixed methods. In detail, we will conduct a single centre, pragmatic, stepped-wedge randomized cluster open-label trial design (27). The units of randomization will be five geriatric rehabilitation units of the ICH (5 clusters). The unit of analysis will be the patient.

All clusters (hospital wards) will begin the study under the control condition. Subsequently, they will be randomly assigned to the intervention at predetermined time points in a sequential, staggered manner until all clusters receive the intervention (see Figure 1).

**Figure 1 fig1:**
[figure not shown]
Stepped-wedge trial design. C, cluster; 0, control; 1, intervention. Each square includes 10 patients.

The computer-generated stepwise randomization of clusters will be carried out with the statistical software R with a randomization seed 184.

For the identification of barriers and enablers for the implementation, we will follow qualitative analysis combining techniques of semi-structured interviews and focal groups.

Trial registration (clinical trial number): NCT07015112 (June 10, 2025).

### Study setting

The study will be developed in an urban ICH “Parc Sanitari Pere Virgili,” Barcelona, Spain. The facility includes 360 inpatient beds, divided into geriatric rehabilitation, subacute care, palliative care, and long-term care, and approximately 40 hospital-at-home beds.

Patients will be included from the five geriatric rehabilitation wards. Most of the admitted patients usually come from a hip fracture or a stroke, or they are admitted following a stay in an acute care ward. The medical staff consists of geriatricians and general practitioners, and multidisciplinary team includes nurses, pharmacists, physiotherapists, occupational therapists, psychologists and social workers, among others. The average length of stay per patient is around 30 days.

### Inclusion and exclusion criteria

Inclusion criteria: older adults (≥65 years), admitted to geriatric rehabilitation units, with 3 or more chronic conditions requiring pharmacological therapy, able to speak Spanish and with the capacity to provide informed consent (or with a carer able to consent on their behalf), under the care of a multidisciplinary team, including geriatricians.

Exclusion criteria: inability to provide informed consent, anticipated length of hospital stay <72 h, or estimated life expectancy <3 months, homeless, patients already enrolled in a drug trial.

Participants who meet the inclusion criteria will be selected upon admission until the necessary sample size is reached.

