
We also acknowledge certain limitations and risks. First, the 90-day follow-up after discharge may vary among the patients, as some may stay at the ICH for longer or shorter periods, influencing the likelihood of following the appropriate therapeutic regimen. Also, we will not conduct specific interventions addressing the various geriatric domains (e.g., cognitive, affective, functional, nutritional), which would vary case by case and could likewise potentially confound the primary and secondary outcomes of the study, also considering the broad inclusion criteria. Moreover, as a monocentric study and the use of a reduced number of clusters, the reproducibility of our findings may be limited. The inclusion of additional centers could have strengthened the potential validity of the evidence deriving from the study. Additionally, given the multidisciplinary nature of the intervention, the applicability and reproducibility of the results in hospitals that are not specifically organized to provide comprehensive assessment and care of older people cannot be assumed and may be limited.

While our hospital maintains stable teams for each ward, we recognize that certain situations could lead to a risk of contamination. If the research team identifies a significant risk in this regard, recruitment may be withhold until the situation stabilizes.

Finally, regarding the sample size, statistical power was set to 75% for the primary outcome in order to guarantee viability of the project and we used previous data from a single center study. Thus, the results will have to be interpreted taking into consideration a possible overestimation of the effect.

Nonetheless, we also acknowledge several strengths. First, its mixed-model design, which is quite original in the literature. Additionally, the use of clusters may facilitate the implementation of the model. Furthermore, considering medications from both qualitative and quantitative perspectives, along with potential ADE/ADWEs, is crucial to enhancing the scientific value of the study, and providing more information on the model’s efficacy and safety.

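### The two consent criteria conflict, and enrolment after the ward's phase is set need not be consecutive, so case mix could differ between control and intervention phases

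*Protocol article*

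**What the plan says.** All references are to the protocol article.

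- **Inclusion and exclusion criteria, consent.** The inclusion criterion asks for capacity to consent, "or with a carer able to consent on their behalf". The exclusion list opens with "Exclusion criteria: inability to provide informed consent", without mention of a carer.
- **Inclusion and exclusion criteria, selection.** "Participants who meet the inclusion criteria will be selected upon admission until the necessary sample size is reached".
- **Design.** The authors state that "we will conduct a single centre, pragmatic, stepped-wedge randomized cluster open-label trial design". "All clusters (hospital wards) will begin the study under the control condition", and wards then cross over in random order. The caption of Figure 1 gives 10 patients per ward-period.
- **Data analysis.** The mixed model names time and cluster. Analyses are to be stratified by frailty and age where appropriate, and a separate multivariable analysis looks at determinants of the decrease in medications.
- **Blinding.** The only blinding described is that of the committee adjudicating adverse drug events and withdrawal events (Participant timeline and data collection).

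**The concern.** Randomising wards to crossover times protects the comparison only if the patients who enter a ward do not depend on its phase. Here each patient is enrolled after the phase is fixed, in an open-label trial, so no allocation concealment operates at patient level.

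Two features of the text leave room for enrolment to differ by phase. The consent criteria give opposite answers for the same patient, so two recruiters, or one recruiter in two phases, can both follow the text and decide differently. The selection sentence sets a stopping point (the target number) but does not require the next eligible admission to be taken.

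The phases also differ in what they ask of patients. The patient-reported outcome interview at admission is described for the intervention phase, and the intervention itself elicits attitudes and preferences. That could make communicative patients easier to enrol there.

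At stake are the primary outcome (mean number of medications per patient) and the trial population. Wards admit mainly after hip fracture, stroke or an acute stay, and cognitive impairment and delirium are both measured, so patients without capacity are unlikely to be rare.

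**Working it through.** **1. The consent rules side by side**

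| Patient | Inclusion criterion | Exclusion criterion | Result |
|---|---|---|---|
| Has capacity | met | not triggered | eligible |
| Lacks capacity, carer can consent | met through the carer | triggered as written | both eligible and excluded |
| Lacks capacity, no carer can consent | not met | triggered | excluded |

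Only the middle row is contradictory.

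**2. The plan's own figures**

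Inputs from Sample size and recruitment: 5 clusters, 10 patients per cluster and time, baseline plus five later times, a decrease of 1.31 from 8.81 medications, ICC 0.2, 300 subjects, power 75%.

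- Size: 5 × 6 × 10 = 300, as stated. With one ward crossing at each step, 15 of the 30 ward-periods are in each phase, or 150 patients per phase.
- Power: no standard deviation is given, so 75% can be neither confirmed nor refuted. With the Hussey–Hughes variance and a two-sided 0.05 normal test, 75% corresponds to an SD of about 2.74.
- Standard error implied by the stated power, two-sided: 1.31 / (1.960 + 0.674) = 0.497 medications.

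**3. Why time and cluster terms do not help**

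Write the model as outcome = period effect + ward effect + θ × phase + error. Suppose patients enrolled in the intervention phase differ by b medications at admission and the difference carries through to the final count. The term b × phase then has the same pattern as θ × phase, so the estimate centres on θ + b. Period and ward terms absorb none of it. Intention-to-treat governs how enrolled patients are analysed, not who is enrolled.

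**4. Illustrative size**

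The values of b are assumptions; none comes from the document. They suppose that final counts are compared without adjustment for admission counts. Share of target = b / 1.31. With no true effect, the two-sided false-positive rate = Φ(b/0.497 − 1.96) + Φ(−b/0.497 − 1.96).

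| Assumed b | Share of 1.31 | False-positive rate |
|---|---|---|
| 0 | 0% | 5% |
| 0.2 | 15% | 7% |
| 0.5 | 38% | 17% |
| 1.0 | 76% | 52% |

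One way to reach such values: if the share of one patient type differs by 10, 20 or 30 percentage points between phases, and that type takes 2 more or 2 fewer medications, then b = 0.10 × 2 = 0.2, 0.20 × 2 = 0.4 or 0.30 × 2 = 0.6 in absolute size.

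**5. Direction**

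The intended effect is a lower count. Fewer medications at entry in the intervention phase would mimic benefit. More at entry would mask it: with a true decrease of 1.31 and an excess of 0.5, the estimate centres on 1.31 − 0.5 = 0.81, and power falls from 75% to Φ(0.81/0.497 − 1.96) = Φ(−0.33), about 37%.

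**The case against.** The consent wording is the same in both phases, so it does not by itself create a difference between them. The carer provision suggests that the exclusion was meant for patients with no one able to consent. The selection sentence is compatible with taking patients in order of arrival; nothing says that recruiters may choose among eligible patients, and a journal article commonly leaves screening procedures to the full protocol. No section says who recruits, so their knowledge of the phase is inferred. Frailty, comorbidity, cognition and medication are recorded at baseline, so imbalance in them would be visible, and stratification by frailty and age is foreseen.

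Much of this stands. The contradiction is an opening for phase-dependent decisions, not proof of them. The likely intent is a reasonable guess, but the text does not state it, and a contradiction in printed criteria is not a detail left out for brevity. That recruiters know the phase remains an inference, though a strong one in an open-label trial where whole wards change practice. Recording baseline variables reveals an imbalance in what is measured; it does not prevent one, and the stated model does not adjust for it. Stratification only where appropriate is not a commitment for the primary comparison.

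**Conclusion.** The point holds in a limited form. The consent criteria contradict each other for patients without capacity who have a consenting carer. Enrolment after the phase is set, with no stated requirement that it be consecutive, allows case mix to differ by phase, and time and cluster terms would not remove that. The document supports neither a size nor a direction. The range of 15% to 76% of the target rests on assumed shifts of 0.2 to 1.0 drugs that carry through unadjusted to the final count.

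A reader might infer three stronger things that the document does not support.

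- **That the ward order is already exposed by the printed seed.** The article says that randomisation "will be carried out with the statistical software R with a randomization seed 184", but dates neither the draw nor the publication of the seed. The seed alone does not fix the order: with seed 184, `sample(1:5)` gives 3 4 2 5 1, `order(runif(5))` gives 2 1 3 4 5, and `sample(1:5)` with R's older rounding sampler gives 2 1 5 3 4. Code and ward coding would also be needed. No new draw is warranted on this ground.
- **That the team may pause enrolment at will.** The Discussion says "recruitment may be withhold until the situation stabilizes", but ties this to a significant risk of contamination. It is a conditional safeguard.
- **That selection would necessarily favour the intervention.** Enrolling patients with more medications in the intervention phase would raise the raw count and work against the intervention.

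**What to change.** 1. Reconcile the two consent statements into one rule, applied identically in both phases. If carer consent is intended, limit the exclusion to patients for whom neither they nor a carer can consent.
2. State that the first 10 consecutive eligible admissions in each ward-period are enrolled, in order of admission, and keep a screening log by phase that records eligible patients not enrolled and the reason.

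Adjusting the primary model for the admission medication count would be a useful addition, but it does not replace these steps, because it corrects only for what is measured.

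The cost is one reworded criterion, one sentence on selection, some logging work and less flexibility for recruiters. The change belongs before further enrolment, since selective recruitment is hard to repair afterwards.
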